## Abstract

**Background:**

The number of abortions worldwide continues to rise, and abortion can have adverse physical and psychological effects. At present, there is little attention paid to the psychological distress experienced by women after abortion, such as anxiety and depression. Current interventions rely heavily on specific personnel, time, and location, which can be costly. Artificial Intelligence-Empowered Mobile Health can compensate for the shortcomings of current interventions, and these interventions are guided by Swanson’s Theory of Caring.

**Methods:**

This study is a mixed-methods research protocol to be implemented at the Inner Mongolia Maternity and Child Health Care Hospital. A total of 100 women after abortion will be included and randomly assigned to either the intervention group or the standard care group. The intervention group will receive two weeks of Artificial Intelligence-Empowered Mobile Health intervention guided by Swanson’s Theory of Caring, including medical knowledge about abortion, post-operative diet, and exercise guidance. The standard care group will receive standard prenatal care. The primary outcome is the change in depression levels, while secondary outcomes include anxiety, perceived stress, perceived social support, and other factors. This study uses IBM SPSS Statistics 27.0 and NVivo 12.0 for data analysis, employing descriptive statistics, normality tests, Mann–Whitney U, Wilcoxon, and chi-square tests.

**Discussion:**

This study pioneers an Artificial Intelligence-Empowered Mobile Health guided by Swanson’s Theory of Caring, providing continuous post-abortion support to reduce psychological distress. It applies Large Language Models to Artificial Intelligence-Empowered Mobile Health for women experienced abortion, delivering timely, specialized care. This approach overcomes traditional barriers: offering real-time interaction, breaking spatiotemporal limits, lowering costs, and integrating expert knowledge to mitigate regional resource disparities, and also promoting health equity.

## Background

1

Miscarriage is generally defined as the loss of a pregnancy before viability. Abortion is a simple health care intervention that can be effectively managed by health workers through medication or surgery. Medical abortion involves using drugs to reduce the biological activity of progesterone and then inducing strong uterine contractions to expel the pregnancy tissue from the body. The drugs commonly used in clinical practice are mifepristone and misoprostol (1). Surgical abortion involves removing the contents of the uterus through the vagina. Different techniques are used depending on the length of pregnancy. Common techniques include manual or electric vacuum aspiration and hysteroscopy (2).

Approximately 73 million abortions are performed worldwide each year. Six out of ten (61%) of all accidental pregnancies and three out of ten (29%) of all pregnancies are terminated by abortion (3). About 10.8% of women experience at least one miscarriage in their lifetime, 1.9% experience two, and 0.7% experience three or more (4). It is estimated that there are about 1.034 million abortions in the United States each year (5), while the total number of abortions in China is estimated to be about 13 million (including cases not fully counted by private hospitals and clinics). Furthermore, since 2017, the number of abortions in China has been increasing annually (6).

Insecure abortion procedures or improper postoperative care can easily lead to hemorrhage and infection. In developing countries, unsafe abortions are one of the main direct causes of maternal mortality (7). Abortion can also affect future pregnancies. Women with a history of abortion have an increased risk of premature delivery and are more likely to experience placental abnormalities (such as placenta praevia, placental abruption, etc.) (4).

Abortion can also have adverse psychological effects on women. Women may experience post-traumatic stress disorder, stress, anxiety, and depression after an abortion (8). Over 60% of interviewees reported occasional or frequent depression and anxiety after abortion (9). Moreover, these psychological distress symptoms persist for longer periods, lasting 14 to 31 months after the abortion (10). After an abortion, women may feel stigmatized due to societal controversy, leading to feelings of guilt, self-blame, or shame, which may exacerbate symptoms of depression, trauma, and anxiety (11).

Abortion costs affect individuals, the healthcare system, and society. It is estimated that the short-term economic loss caused by abortion in the UK each year amounts to £471 million (4). Complications arising from unsafe abortions require a higher level of care (12), which not only increases treatment costs, leading to financial losses for individuals and consumption of medical resources (13), but also causes labor losses (14). In addition, abortion bans in some countries and regions will increase public expenditure, such as medical subsidies (15).

Current attention to psychological distress after abortion is insufficient. Routine intervention relies heavily on medical staff to provide preoperative explanations, post-operative structured counselling (16), and partner support or mutual-help groups (17). However, such medical resources are severely lacking in remote and underdeveloped areas. Some patients refuse post-operative follow-up due to financial constraints, resulting in their inability to accept structured psychological counselling. Current intervention methods require advanced planning and are conducted at fixed times and locations. However, the emotional distress is often sudden and unpredictable, making it difficult for traditional offline interventions to provide immediate emotional support, which may exacerbate the condition. Developing online intervention methods can compensate for the aforementioned shortcomings, but research in this field remains largely unexplored. Wang et al. developed an online short-term intervention for patients who had undergone abortions based on stress coping theory, which improved psychological well-being by enhancing self-efficacy and social support. The results showed that two weeks after the abortion, the intervention group had significantly lower depression scores, improved problem-coping abilities, and held more positive perceptions of their abortion experiences (18).

Mobile health is “medical and public health practices supported by mobile devices, such as mobile phones, patient monitoring devices, personal digital assistants (PDAs), and other wireless devices.” (19) The application of mobile health in medicine is becoming increasingly widespread. Its main advantages are that it can break through the limitations of time and space, is inexpensive to use, and can provide fast, rich, and personalized medical information (20).

Large language models (LLMs) are complex neural network models based on deep learning, specifically designed to understand, process, and generate human-like natural language. They are trained on massive amounts of text data, learning statistical patterns and contextual relationships within the text to accomplish tasks (21). At present, commonly used LLMs internationally include ChatGPT, etc. Recently, LLMs in China have gradually developed, and models such as DeepSeek, Doubao, and Kimi have also gained recognition and widespread application in China. The application of LLMs in medicine includes simplifying complex medical information, integrating patient data, assisting doctors in clinical diagnosis and decision-making, and performing common medical and health tasks such as health education and emotional support for patients through the generation of high-quality, human-like interactive text (22).

LLMs are primarily deployed on Personal Computers (PCs) and some mobile devices, with deployment methods depending on model size, optimization level, and mobile device hardware capabilities (23). Successfully deploying a fully functional LLM on mobile phones can combine its exceptional natural language processing capabilities with the advantages of mobile health, which breaks through spatial and temporal limitations.

Coze is a new-generation AI agent development platform developed by ByteDance, enabling the rapid creation of various AI applications based on LLMs. With its modular workflow engine and robust knowledge base construction capabilities, it effectively mitigates the phenomena of “hallucination” or “fabrication” in LLMs (24), ensuring the accuracy of responses in professional domains. The platform supports users uploading their databases, allowing agents to complete self-learning based on this data. Through its one-click deployment function, AI agents can be deployed to WeChat Official Accounts, leveraging WeChat’s over 1.4 billion active users to provide precise services for professional settings.

Swanson’s Theory of Caring was developed by British scholar Swanson, whose theoretical framework integrates the core findings of three independent phenomenological studies. Swanson’s Theory of Caring emphasizes that nurses are the primary implementers of patient care, possessing a high degree of independence and not merely serving as assistants to doctors. The theory posits that nurses’ care and concern for patients have a positive impact on patient health that is no less significant than the therapeutic interventions. Its core framework consists of five care behaviors: knowing, being with, doing for, enabling, and maintaining belief (25).

Knowing: Nurses assess patients’ needs and physical and psychological status thoroughly. Knowing patients well is the basis for personalized care. But be careful not to be prejudiced. Use a variety of comprehensive assessment methods and focus on patients’ concerns and confusion.Being with: Being with someone is a step beyond knowing them. Nurses in clinical settings focus on emotional support, which can be done by being physically present with patients, encouraging them to express their feelings, sharing their own experiences and feelings with patients, and responding appropriately. This helps patients feel cared for, supported, and understood.Doing for: This typically refers to nurses providing professional care to patients and offering practical assistance, such as pain management and technical guidance. However, excessive intervention is not recommended.Enabling: Nurses need to use their professional knowledge to provide patients with information and explanations through education and resource provisioning, offer emotional support, and enhance patients’ self-care abilities.Maintaining belief: Nurses need to help patients maintain hope, enable them to get through events or turning points, and face the future positively.

Currently, Swanson’s Theory of Caring is widely applied in studies involving women who have experienced abortion. Jansson et al. (26) conducted semi-structured interviews with women who experienced early abortion or missed abortion between 18 and 20 weeks of pregnancy. The researcher analyzed the data using the five processes of Swanson’s Theory of Caring. The results indicated that care beneficial to women includes empathy, emotional support, maintaining dignity, competence, and meeting individualized needs. Adolfsson et al. (27) applied Swanson’s Theory of Caring to the rehabilitation of women who experienced early miscarriage. The results indicated that midwives who followed up with women after miscarriage using this theory as a guide were able to reduce sadness scores. Palas et al. (28) found that personalized care based on Swanson’s Theory of Caring could alleviate patients’ physical, emotional, behavioral, and cognitive sadness symptoms, as well as reduce future negative emotions, depression, and anxiety.

The study aims to evaluate the effectiveness of an Artificial Intelligence-Empowered Mobile Health intervention using Swanson’s Theory of Caring on negative psychological states such as depression and anxiety in women after abortion through a mixed-methods study, while also examining clinical examination and test indicators and semi-structured interview data from patients.

The specific objectives are:

To evaluate whether the two-week AI mobile health intervention program reduces psychological distress in women after miscarriage.To evaluate the acceptability of an AI-based mobile health intervention in primary care for women after abortion.

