### Design

2.1

The study will use a mixed-methods study design and will be conducted at the Inner Mongolia Maternity and Child Health Care Hospital from 2025 to 2026. A randomized controlled trial with two parallel groups will compare the effectiveness of an Artificial Intelligence-Empowered Mobile Health intervention guided by Swanson’s Theory of Caring on psychological distress (such as depression, anxiety, and stress) in women after abortion. The intervention will last for two weeks, with participants undergoing questionnaires, physical examinations, and individual interviews at baseline and at two weeks to explore changes in psychological distress. The study flowchart is shown in **Figure 1**.

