#### Exclusion criteria

2.2.2

Involuntary abortion or unclear pregnancy intentions;Severe physical complications after abortion (such as massive bleeding, infection, etc., requiring hospitalization);Individuals with mobility issues, impaired consciousness, or mental disorders;Individuals with tumors who have undergone radiotherapy or chemotherapy in the past six months;Inability to understand or complete questionnaires in Chinese;Currently participating in other similar research studies;Unwilling to cooperate.

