#### Control group: standard care

2.5.1

The control group was not completely blank. At the time of enrolment, patients in the control group received standard oral health education, including explanations of the surgical procedure and precautions, routine preoperative examinations, and guidance on postoperative precautions. Any questions or concerns raised by patients were answered in detail.

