**Specific Methods:**

Staff Introduction: Introduce the attending doctor and nurse during the first consultation to establish comfort and familiarity.Detailed Explanation: Provide an everyday language explanation of the purpose of the examination and important considerations. For example, a blood routine is conducted to exclude anemia and ensure safety, and an ultrasound requires holding urine and drinking water beforehand. Visualize medical reports, such as describing “a gestational sac size of 5 cm” as “the size of an egg, consistent with the gestational age.”Body Language: Use eye contact, physical touch, and accompany patients during waiting periods to alleviate anxiety and feelings of loneliness.Provide Support Tailored: Explain medical insurance policies and exemption procedures in person for economic difficulties, provide dialect interpretations (with QR codes) and handwritten versions of important notes for those with lower educational levels.Empowerment Through Similar Cases: Provide successful case examples with similar clinical and social backgrounds to enhance patients’ confidence and courage in recovery.

**Phase 2: Two weeks after surgery and before follow-up examination**.

**Swanson’s Theory of Caring:** Knowing.

**Intervention providers:** Attending doctor, researcher.

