**Specific Methods:**

Communication Time: One week after the patient’s abortion, online communication via telephone, WeChat, or other platforms, lasting approximately 20 minutes.Communication Content: Comprehensive understanding of the patient’s physical recovery, inquiring about fever, foul-smelling secretions, bleeding, abdominal pain, etc., assessing the patient’s psychological state, whether there are negative emotions such as inferiority, anxiety, depression, or despair, recognizing the patient’s additional needs for post-operative health knowledge.

**Swanson’s Theory of Caring:** Doing for, Enabling.

**Intervention providers:** Researcher.

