**Specific Methods:**

Contact the patient proactively before the follow-up examination to reconfirm the time, location, and examination items.Accompany the patient throughout the follow-up examination on the day of the appointment, explaining the environment and the purpose of each examination to alleviate any feelings of unfamiliarity.Pay attention to the patient’s emotions, provide patient companionship and positive support, and encourage them to face the future with optimism.

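### The randomised contrast is a staff-plus-AI care package against standard care, but the first objective and the section 2.5.2 heading present it as AI added to standard care, and the objective misnames the population

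*Protocol article*

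**What the plan says.** **What is named as tested.** The Background gives two objectives: "To evaluate whether the two-week AI mobile health intervention program reduces psychological distress in women after miscarriage" and "To evaluate the acceptability of an AI-based mobile health intervention in primary care for women after abortion". Section 2.1 states that "A randomized controlled trial with two parallel groups will compare the effectiveness of an Artificial Intelligence-Empowered Mobile Health intervention guided by" the caring theory. The heading of section 2.5.2 labels the intervention arm as standard care plus AI-empowered mobile health, and the text below it calls the AI service the core method.

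**What the control arm receives.** Under section 2.5.1, "patients in the control group received standard oral health education" at enrolment. This covers the procedure, preoperative examinations and postoperative precautions, and questions are answered.

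**What the intervention arm receives from people.** Section 2.5.4 names the attending doctor and researcher, or the researcher alone, as providers of each block. Three elements need no AI:
- Phase 1: "Use eye contact, physical touch, and accompany patients during waiting periods to alleviate anxiety and feelings of loneliness", together with examples of similar patients who did well.
- Phase 2, one week after the abortion: "online communication via telephone, WeChat, or other platforms, lasting approximately 20 minutes", covering physical recovery and psychological state.
- Phase 3, at the follow-up visit: the researcher accompanies the patient throughout and is to "provide patient companionship and positive support, and encourage them to face the future with optimism".

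**Population.** Section 2.2.1 requires surgical abortion before the 14th week of pregnancy. Section 2.2.2 excludes "Involuntary abortion or unclear pregnancy intentions".

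**The concern.** The label and the content of the intervention arm do not match. A reader of the objective and the arm heading would take a lower PHQ-9 score as evidence that the AI service works. The arms also differ in personal contact aimed directly at anxiety, loneliness and low mood, which are close to what the outcome scales measure.

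The protocol gives reason to think this contact is active. The Background reports that midwife follow-up guided by the same theory reduced sadness, and that personalised care based on it reduced depression and anxiety. Section 2.3 takes nursing interventions based on the theory, not an AI tool, as its reference for effect size.

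At stake is what a positive trial may conclude. The Abstract and Discussion argue for the AI service on low cost, independence of time and place, and relief of scarce staff resources. Those arguments depend on the AI doing the work, and this comparison cannot show that.

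The first objective also concerns women after miscarriage. The Background defines miscarriage as loss of a pregnancy before viability and treats abortion as a health care intervention, so the word points to women whom the exclusion criteria keep out.

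**Working it through.** The point rests on comparing the content of the two arms. The protocol has no figure to reproduce for it.

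**Step 1. Arms side by side.**

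| Element | Intervention arm (2.5.4) | Control arm (2.5.1) |
|---|---|---|
| Education, preoperative examinations, postoperative precautions, answers to questions | Yes, as standard care | Yes |
| AI service through the WeChat account | Yes | No |
| Touch, accompaniment while waiting, similar cases | Yes, doctor and researcher | None described |
| Personal contact of about 20 minutes at one week | Yes, doctor and researcher | None described |
| Accompaniment and encouragement at follow-up | Yes, researcher | None described |

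Some elements are left out because they are not clearly both non-AI and confined to one arm:
- The daily WeChat messages direct patients to the AI agent.
- The one-on-one guidance in Phase 1 is instruction in using the service.
- Section 2.1 mentions individual interviews for participants generally.
- Section 2.8 promises self-care guidance throughout the study without limiting it to one arm.
- Controls also attend the baseline and two-week assessments.

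**Step 2. What the contrast estimates.** Apart from chance, the difference between the arms is the joint effect of AI access and the three staff-delivered elements, including any interaction. With two arms, and AI and contact always given together, there is one contrast and at least two unknowns. No sample size or analysis model separates them. The qualitative interviews ask about AI functions, but they are not a randomised comparison.

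**Step 3. Timing.** Section 2.5.4 places completion of the follow-up questionnaires in Phase 3, the phase in which intervention patients are accompanied. The undescribed counterpart in controls therefore falls close to measurement of the primary outcome.

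**Step 4. Illustration.** Inputs from section 2.3: SD 8, 50 per group, two-sided 5% level (Z = 1.96). Assumptions, not in the protocol: the AI has no effect, and staff contact alone lowers PHQ-9 by c points.

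Standard error = 8 × √(2/50) = 1.6. The chance of a significant result favouring the intervention is Φ(c/1.6 − 1.96).

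| c (points) | c/1.6 − 1.96 | Chance, 50 per arm | Chance, 42 per arm |
|---|---|---|---|
| 2 | −0.71 | 24% | 21% |
| 3 | −0.085 | 47% | 40% |
| 4 | 0.54 | 70% | 63% |
| 5 | 1.165 | 88% | 82% |

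The last column uses the 42 per group that section 2.3 states before its allowance for loss, with standard error 8 × √(2/42) = 1.75.

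**Step 5. Population.** The overall aim and the second objective in the Background speak of women after abortion. Sections 2.2.1 and 2.2.2 agree with them. Only the first objective says miscarriage.

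**The case against.** The strongest reply is that testing a multicomponent package against standard care is legitimate, and that the protocol partly discloses one. The first objective speaks of a program, the aim and the design statement tie the AI service to the caring theory, section 2.5.2 calls AI the core method and not the only one, and section 2.5.4 lists human providers phase by phase. This stands. A reader might infer that the comparison is invalid, and the documents do not support that: it answers whether the package works.

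A reader might also infer that the protocol claims a service without staff. No section does. Staff review the interaction logs, contact physicians and follow patients up, and the remarks on cost and reliance on personnel read as rationale. Nor do the documents support a picture of controls who receive a single session and nothing else, given the shared assessments and section 2.8.

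It may be tempting to ask that all non-AI contact be given to both arms. That would replace the standard-care comparator, and the expected effect would no longer be the one for which section 2.3 cites caring-theory nursing care. It is a different trial.

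The illustration can be criticised because the protocol gives no effect for contact alone. That is correct. It shows what could happen under stated assumptions and estimates nothing.

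None of this removes the three elements in the table, and the heading of section 2.5.2 does not mention them.

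**Conclusion.** The concern holds as a mismatch between what is named and what is compared. The trial can support a conclusion about a combined package of theory-guided staff care and an AI service against standard care. It cannot support a conclusion about the AI component, whatever the p-value.

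The share of any effect due to the AI is not estimable from this design, so no figure or bound is given for it. It would go too far to say that an observed benefit must come from the staff. The documents show only that it could, and that the protocol itself regards such care as effective.

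This rests on one assumption: that the control arm receives no counterpart to the three elements, as section 2.5.1 reads. If the full protocol gives controls the same contact, the attribution point weakens accordingly.

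The miscarriage wording is a separate, smaller contradiction in the same sentence. It does not mean that the wrong women will be enrolled, because the eligibility criteria and the second objective are consistent with each other.

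**What to change.** Reword the first objective, the heading of section 2.5.2, the primary comparison and the planned conclusions so that they describe a Swanson-guided care package that includes an AI mobile health service, compared with standard care, in women having voluntary surgical abortion before the 14th week. This also removes the reference to miscarriage.

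Add a sentence to the design section and the limitations stating that the trial does not isolate the effect of the AI service, and that the arguments on cost and reliance on personnel are rationale and not conclusions under test.

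The change needs no extra patients, visits or analyses. Its cost is a narrower claim: a positive result would support the package and not the AI on its own.
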